### Randomization, blinding and stratification procedures

We will use a computer-generated randomization sequence. Only the CHEO pharmacy will have access to the randomization sequence and will be responsible for participant randomization and allocation. Only the pharmacist will know the identity of the study drug administered to specific patients. Given the expected recruitment (two to three per month) and potential impact of season on 25OHD, randomization will be performed in permuted blocks (four within each stratum). We will blind patients, families, investigators, hospital staff, and research personnel to treatment arm. Blinding was considered necessary to avoid (i) families altering the outpatient dose and (ii) a number of secondary outcome measures are that are potentially subjective (echocardiography, timing of extubation, need for fluids or catecholamine infusion). Within each age group, the two interventions will be indistinguishable (vial, volume, color, taste, consistency and smell).

Participants will be stratified into whether or not they are expected to receive at least 8 weeks of study drug prior to surgery. This stratification should guarantee that an equal number of CHD patients who will not receive 8 weeks of oral dosing end up in both the high and low dose arms. We will further stratify by age (under or over 1 year of age).

### Co-interventions

We will not protocolize postoperative co-interventions as the study is single center and CHEO has standardized approaches to the common postoperative complications and adverse events (for example, hypocalcemia, junctional ectopic tachycardia, necrotizing enterocolitis constipation, sedation, catecholamine administration, *etcetera*). As the study is blinded, protocolization of co-interventions is less relevant and differences should relate to random chance or drug effects.

### Diagnostic and clinical outcome measures

#### Blood 25OHD

The primary objective will be evaluated using immediate postoperative blood 25OHD concentrations (collected on the day of ICU admission) with a level lower than 50 nmol/L used to define deficiency [61, 62]. This is a well-established cut-off based on (i) the knowledge that the parathyroid and renal organs need to compensate for 25OHD levels below 50 nmol/L and (ii) clinical studies that have shown increased risk of bone, cardiovascular, immune and other disease entities once concentrations fall below this level. The 25OHD will be determined using a LC-MS/MS assay from a laboratory participating in the Vitamin D External Quality Assessment Scheme (DEQAS) [22, 63].

#### Vitamin D-related adverse events

We will report, by intervention, on the occurrence of clinically significant adverse events. However, a measurable difference in clinically significant adverse events between the high dose and usual care arms of the study is unlikely. Therefore, to enhance our ability to evaluate for potential toxicity, we will use two well-accepted surrogate outcome measures:*Hypercalcemia:* This will be defined as an ionized calcium level above 1.40 mmol/L (or above 1.45 mmol/L for children under 8 weeks) (Table 3). We will evaluate for hypercalcemia in blood collected immediately before surgery and throughout the postoperative course (measurements are a standard of care, and any single episode of hypercalcemia not related to parenteral administration of calcium will be considered an adverse event) [64].

**Table 3 Tab3:** Safety thresholds for ionized calcium, total corrected calcium and elevated calcium-creatinine ratio

Table 3A: Age specific thresholds for pH corrected ionized calcium levels	
Age (months)	95th % (mmol/L)
<2	1.45
>2	1.4
Table 3B: Threshold for corrected total calcium level	
Age (months)	mmol/L
<3	2.8
>3	2.7
Table 3C: Age specific thresholds for elevated calcium-creatinine ratio	
Age (year)	95th % Ca/Cr ratio (mmol/mmol)
<1	2.2
1–2	1.5
2–3	1.4
3–5	1.1
5–7	0.8
7–17	0.7*Hypercalciuria -* We will identify hypercalciuria using calcium:creatinine ratios defined using age-specific norms and thresholds (Table 3) [64–66]. Measurements will be performed on urine collected in the operating room immediately prior to surgery and on the first postoperative day.

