**Fig. 1 Fig1:**
[figure not shown]
Flow chart of study-related procedures and measurements. Patients and/or caregiver may decline initiation blood work and urine samples and still participate. Postoperatively, urine will only be collected at PICU admission if it was not collected in the operating room. Participants with isolated postoperative hypercalciuria will only have renal ultrasound at the request of nephrology. CHD, congenital heart disease; PICU, Pediatric Intensive Care Unit; POD, postoperative day

**Table 4 Tab4:** Biochemical measurements on research specimens

Sample	Timepoint				
	Pre-treatment^a^	During study drug administration^b^	Preoperative^c^	Operating room prior to surgery	Postoperative
Blood	Vitamin D^d^	Vitamin D^d^	Vitamin D^d^	Vitamin D^d^	Vitamin D^d^
		Ionized calcium	Ionized calcium	Ionized calcium	Ionized calcium
				VDBP	VDBP
				PTH	PTH
				Immune function	Immune function
				(for example, cathelicidin)	(for example, cathelicidin)
				Immune activity	Immune activity
				(for example, cytokines)	(for example, cytokines)
Urine	Calcium to	-	-	Calcium to	Calcium to
	Creatinine ratio			Creatinine ratio	Creatinine ratio

^a^neonates, or < 2 months of supplement anticipated

^b^any patient who receives > 6 months of supplement

^c^all outpatients who receive > 2 months of supplement

^d^25OHD will be measured to indicate vitamin D status. The 25OHD level determined at the time of standard preoperative blood work, for safety purposes, will be ordered through the laboratory. The intraoperative and postoperative 25OHD measurements will be determined, using LC-MS/MS technology that adheres to and meets the standards of the Vitamin D External Quality Assessment Scheme

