#### During period of study drug administration

All outpatient participants will have blood collected at the time of standard presurgical blood work (2 to 3 weeks prior to surgery) for both 25OHD and ionized calcium. These samples are collected to ensure that patients do not go for surgery with potentially toxic levels of vitamin D. The safety officer will review the ionized calcium level on the patients chart, and follow up if required, as per the safety measures outlined in the sections below. For those participants who will receive the study drug for more than 6 months, we will measure 25OHD and calcium, and they will also have additional blood work to ensure that potentially toxic levels are not maintained for long periods prior to surgery. The timing of this blood work will not be specified and will occur as part of clinically indicated blood work during regularly scheduled clinic appointments

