#### Intraoperative biological samples and measurements

**Blood** - All study participants will have 2 mL of blood collected in the operating room following anesthesia and intubation, but prior to skin incision and initiation of cardiopulmonary bypass. Preoperative ionized calcium will be determined. Remaining sample will be aliquoted and stored at -80 °C for determination of 25OHD at the end of the study.

**Urine** - All study participants will have urine collected after insertion of the urinary catheter and the calcium:creatinine ratio will be determined. Study results will not appear on the patient hospital chart, but will be labeled with the study ID number and forwarded to the study investigator and safety officer for review.

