### Safety measures and clinically relevant research findings

A flow diagram depicts the safety measures in place and response to clinically relevant research findings for individual study participants (Additional file 3). A standard operating procedure has been developed for adherence to the following safety measures.

To avoid vitamin D overdose, hypercalcemia and side effects, we have selected a supplement level recently proven to be safe in healthy children and will target the period of high-dose supplementation to 6 months and no more than 12 months. Study participants with elevated blood calcium and/or vitamin D levels will be identified and contacted by the safety officer. For 25OHD, although 500 nmol/L is generally considered the definitive acute toxicity threshold, we have chosen to intervene with 25OHD levels above 200 nmol/L as this value is supraphysiological and exceeds our study goal. The following details the actions that will be taken with abnormal values:For 25OHD above 200 nmol/L with evidence of hypercalcemia (vitamin D toxicity), discontinue study drug immediately, repeat the values (fasting), and refer to endocrinology.For 25OHD above 200 nmol/L without hypercalcemia, the study drug will be reduced by 50 %; (c) For 25OHD above 250 nmol/L, without hypercalcemia: study drug will be discontinued.For hypercalcemia with 25OHD under 200 nmol/L, repeat the bloodwork (fasting) and refer to endocrinology.

Both postoperative hypo- and hypercalcemia will be managed by the clinical team as required. Study participants with persistently elevated blood calcium levels (for more than 2 days, not explained by intravenous calcium administration) will be referred to endocrinology (Additional file 3).

As prolonged exposure to hypercalciuria (>3 months) could theoretically cause nephrocalcinosis, we will have ultrasounds performed prior to hospital discharge on all patients with elevated immediate preoperative urine calcium to creatinine ratios. Any study participant with nephrocalcinosis will be referred to the nephrology service for further assessment.

Participants that have study drug discontinued or decreased will be retained in the study, have perioperative biological samples collected as outlined, and will be included in the analysis using intention to treat methodology.

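### The between-arm hypercalcemia outcome leaves out the scheduled on-drug calcium results that the safety rules act on, so high-dose toxicity can be understated

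*Protocol article*

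**What the plan says.** The first secondary objective (Study objectives) asks whether the high dose leads to more vitamin D related adverse events, hypercalcemia among them. Because clinically significant events are not expected to separate the arms, the section Vitamin D-related adverse events adopts hypercalcemia as one of two surrogates, with ionized calcium thresholds in Table 3A. Its window is: "We will evaluate for hypercalcemia in blood collected immediately before surgery and throughout the postoperative course". A parenthesis attached to that sentence adds that "any single episode of hypercalcemia not related to parenteral administration of calcium will be considered an adverse event".

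The sample that best fits the first half of this window is described under Intraoperative biological samples and measurements. It is blood "collected in the operating room following anesthesia and intubation, but prior to skin incision and initiation of cardiopulmonary bypass", and ionized calcium is determined on it.

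Two further calcium measurements come earlier, while the child is on study drug (During period of study drug administration):

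- Outpatients have "blood collected at the time of standard presurgical blood work (2 to 3 weeks prior to surgery) for both 25OHD and ionized calcium".
- "For those participants who will receive the study drug for more than 6 months, we will measure 25OHD and calcium". Table 4, footnote b, describes the same group as "any patient who receives > 6 months of supplement".

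Safety measures and clinically relevant research findings says what follows from an abnormal value. With 25OHD above 200 nmol/L and hypercalcemia, the instruction is to "discontinue study drug immediately, repeat the values (fasting), and refer to endocrinology". For the lower range it reads: "For hypercalcemia with 25OHD under 200 nmol/L, repeat the bloodwork (fasting) and refer to endocrinology". With 25OHD above 200 nmol/L and no hypercalcemia, study drug is halved, or stopped above 250 nmol/L. These children stay in the trial and in the intention-to-treat analysis.

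**The concern.** The omitted samples are scheduled during dosing, and the article says their purpose is to keep children from reaching surgery with potentially toxic vitamin D levels. A process meant to find and act on cases therefore runs ahead of the outcome meant to count them. A child who is hypercalcemic at the presurgical check and normal in the operating room scores as no event.

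At stake is the safety half of the trial's purpose. The Background gives the goal as a regimen that safely prevents deficiency, and the abstract says the results will inform a larger trial. The hypercalcemia surrogate was chosen to make toxicity easier to detect, and a window that skips the on-drug results works against that.

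**Working it through.** **1. Which samples fall in the window**

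| Table 4 column | Who | Ionized calcium | In the outcome |
|---|---|---|---|
| During study drug administration | more than 6 months of supplement | yes | no |
| Preoperative | outpatients (Table 4: only with more than 2 months of supplement) | yes | no |
| Operating room prior to surgery | all | yes | yes |
| Postoperative | all | yes | yes |

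Table 4 lists Preoperative and Operating room as separate columns. A check 2 to 3 weeks before surgery is therefore hard to read as blood taken immediately before it.

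**2. Direction**

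The present window is a subset of all scheduled samples from first dose onward. Dropping samples can lower an arm's count or leave it unchanged, never raise it. The difference between arms shrinks if the high-dose arm has more cases seen only on drug, which is the pattern to expect if the dose causes hypercalcemia. If it does not, little is lost.

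**3. The article's own figures**

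Inputs from Sample size justification: 40% versus 80%, two-sided Fisher's exact test, significance level 0.05, 28 per arm, 10% drop-out. Full enumeration gives 82.3% power at 28 per arm, so the stated 80% is met. The total is 56 × 1.10 = 61.6, rounded to 62.

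For hypercalcemia the article says a high-dose rate above 30% would be shown for a baseline of 0 to 10%, without giving a power. Exact Fisher power with 28 per arm:

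- 0% versus 30%: 88.7%
- 5% versus 30%: 57.7%
- 10% versus 30%: 33.2%

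The comparison is already thin unless the baseline is close to zero.

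**4. How many cases it takes**

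With 0 of 28 in usual care and x of 28 in the high-dose arm, the two-sided Fisher p-value is 2 × C(28,x) / C(56,x):

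- x = 6: 2 × 376,740 / 32,468,436 = 0.023
- x = 5: 2 × 98,280 / 3,819,816 = 0.051
- x = 2: 2 × 378 / 1,540 = 0.49

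Six counted cases are needed. Losing one of six already moves the result across 0.05.

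**5. Illustration of the loss**

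The article gives no on-drug hypercalcemia rate. Assume that a share f of cases is seen only at the on-drug checks. The counted high-dose rate is then 0.30 × (1 − f). With 0% in usual care, power is the probability of at least 6 events in 28 at that rate. The last column starts from 5% in usual care and lets both arms lose the same share.

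| f | Counted high-dose rate | Power, true 0% vs 30% | Power, true 5% vs 30% |
|---|---|---|---|
| 0 | 30% | 88.7% | 57.7% |
| 10% | 27% | 80.8% | 49.2% |
| 25% | 22.5% | 62.7% | 35.5% |
| 50% | 15% | 23.5% | 13.5% |
| 75% | 7.5% | 1.6% | 1.1% |

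These rows show sensitivity to f. They do not estimate it.

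**The case against.** Much can be said for the plan as written.

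- **On-drug cases may be reported elsewhere.** Data and safety monitoring names ionized calcium as a source of adverse-event information, with no window, and clinically significant events are to be reported by arm. A reader might infer that on-drug cases vanish from the trial's safety reporting. The article does not support that. What stands is narrower: no sentence places them in the between-arm hypercalcemia outcome.
- **The operating-room reading is an inference.** For urine the article names the operating room; for blood it says only that the sample is taken immediately before surgery. Table 4 and the intraoperative section make the inference strong.
- **The window is not mainly off-exposure.** Study drug runs to the day of operation, so in a child not stopped early the operating-room sample falls at the end of dosing. The trial also expects high-dose children to stay above 50 nmol/L after bypass.
- **Cases may persist to surgery.** Hypercalcemia with 25OHD under 200 nmol/L leads to repeat testing and referral, with no stop stated, in either arm. Only the 200 nmol/L rules should fall mainly on the high-dose arm. The article gives no time course for calcium after a stop.
- **Frequent actions cannot be derived.** Combining the quoted means of 130 to 150 nmol/L with 80% at or above 90 nmol/L gives, under normality, SDs of 47.5 to 71.3 from (mean − 90)/0.8416, and 7% to 24% above 200 nmol/L. A reader might conclude that safety actions will be common. But the means come from healthy children, the 80% is a projection for children with CHD, and a high 25OHD is not hypercalcemia.
- **The perioperative samples cover everyone.** On-drug checks depend on outpatient status and treatment duration. This stands, and the fix has to respect it.

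**Conclusion.** The point holds in a limited form. The outcome omits scheduled on-drug calcium results that can lead to stopping study drug or to referral before the outcome window opens, so it can understate high-dose toxicity. It would be too strong to say that toxicity is understated. That needs cases that resolve before surgery, and the article gives neither their number nor the share that would resolve.

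The illustration rests on 28 per arm, a true high-dose rate of 30% and an assumed share f. Under it, a quarter of cases seen only on drug takes power from 88.7% to 62.7% with no usual-care cases.

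This is a should-fix. It concerns a secondary surrogate in a 62-child pilot, and the primary comparison is untouched. The safety officer's follow-up of on-drug calcium does not depend on how the outcome is defined.

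**What to change.** Reword the hypercalcemia outcome, before unblinding, as follows:

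1. Count any ionized calcium above the Table 3A threshold in any scheduled sample from first dose through the operating-room sample, even if it later normalizes. Limiting this to scheduled samples keeps triggered repeat tests from adding events in one arm.
2. Give the operating-room result its own line, since all participants have it and on-drug sampling varies with outpatient status and treatment duration.
3. Report postoperative hypercalcemia as a separate outcome.
4. Tabulate by arm the children with 25OHD above 200 nmol/L and those whose study drug was reduced or stopped under the safety rules.

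Also reconcile who has the presurgical check. The text gives it to all outpatients, while Table 4, footnote c, limits it to outpatients with more than 2 months of supplement.

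The cost is the wording of one definition and one table. All the values are already collected and no clinical rule changes. Children dosed longer have more chances of a positive result, but the schedule is the same in both arms and randomization is stratified on whether at least 8 weeks of study drug is expected.

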#### Prior to initiation of study drug

**Urine** - After consent is obtained and the study participant is waiting for the pharmacy to prepare the study drug, we will gather a urine sample for determination of calcium:creatinine ratios. Where developmentally appropriate, the participants will be asked to provide urine into a container. Urine bags will be placed on younger children. If the child is unable to provide a urine sample during the time it takes to fill the study drug prescription, the participant will be provided with a container or urine bag and asked to provide an outpatient urine sample.

**Blood** - Neonates and other study participants requiring surgery within 2 months of diagnosis and enrollment will have 0.5 to 1 mL of blood collected prior to (or within 2 days) of starting the study supplement for determination of 25OHD. Where possible, unused or discarded blood will be obtained from the laboratory [68]. If unused blood is not available, research blood will be collected at the time of clinically indicated blood work, or not at all. These patients will not have blood collected for research purposes again until they are taken to the operating room.

* Note - We will request initiation samples but children will still be enrolled if these samples cannot be collected or the families do not want these procedures.

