#### Comments on power for evaluating vitamin D-related adverse outcomes

**Hypercalcemia** - Our previous observational study (n = 58) identified no cases of preoperative or immediate postoperative hypercalcemia [26]. With a baseline rate in the usual care arm between 0 and 10 %, our sample size would be sufficient to show a statistically significant absolute difference between groups if the rate in the high dose arm exceeded 30 %.

**Hypercalciuria** - Information on baseline rates of hypercalciuria prior to or following cardiac surgery with usual care vitamin D intake is not available. The proposed sample size would be sufficient to demonstrate a 35 % absolute difference in proportions if the baseline pre- or postoperative rates are up to 20 %.

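### Table 4 and the procedures text disagree on who gives pre-treatment urine, and the hypercalciuria outcome makes no use of that baseline, which dilutes the safety comparison without biasing it

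*Protocol article*

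**What the plan says.** **Outcome.** Under Vitamin D-related adverse events, hypercalciuria is a calcium:creatinine ratio above the age-specific 95th-percentile limit in Table 3C. The sampling times are fixed: "Measurements will be performed on urine collected in the operating room immediately prior to surgery and on the first postoperative day". Under Secondary outcomes, binary outcomes of this kind are compared between arms by Fisher's exact or chi-square test. Regression is added only if important variables turn out to be unevenly distributed.

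**Pre-treatment urine, procedures text.** Under Prior to initiation of study drug, after consent and while the pharmacy prepares the drug, "we will gather a urine sample for determination of calcium:creatinine ratios". No limit by age or expected exposure is attached. The next paragraph, on blood, does carry one: "Neonates and other study participants requiring surgery within 2 months of diagnosis and enrollment will have 0.5 to 1 mL of blood collected".

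**Pre-treatment urine, Table 4.** The pre-treatment column lists both blood 25OHD and the urine ratio. Its footnote a, on the column heading, reads "neonates, or < 2 months of supplement anticipated".

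**Optional sampling.** The procedures text states "We will request initiation samples but children will still be enrolled if these samples cannot be collected", and the Fig. 1 legend agrees: "Patients and/or caregiver may decline initiation blood work and urine samples and still participate".

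**Background rate.** The comments on power say "Information on baseline rates of hypercalciuria prior to or following cardiac surgery with usual care vitamin D intake is not available". They claim the sample size suffices for a 35-point absolute difference when the pre- or postoperative baseline rate is up to 20%.

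**The concern.** There are two linked defects.

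First, Table 4 and the procedures text cannot both govern the urine sample. Staff working from the table would skip it in children who are not neonates and are expected to take study drug for 2 months or more. These are the children with the longest exposure. The safety section ties its concern about nephrocalcinosis to hypercalciuria lasting more than 3 months, so the baseline would be missing in the children that concern is about.

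Second, a baseline is planned and then given no role. The limit is a 95th percentile, so about 5% of a reference population exceeds it by construction, and the article says the rate in this population is unknown. Children above the limit before the first dose enter the adverse-event count in both arms alongside new cases. Hypercalciuria was chosen as a surrogate to sharpen the assessment of toxicity, so an avoidable loss of power matters: a non-significant result could be read as reassurance when the larger trial is planned.

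**Working it through.** **1. Who would lack a baseline under Table 4.** The section on duration of study drug expects 75 to 80% of patients to receive drug for more than 2 months. Of 56 evaluable children that is 0.75 × 56 = 42 to 0.80 × 56 ≈ 45. About 11 to 14 would then have a baseline, plus any neonates with longer expected exposure, whom footnote a also covers. Under the procedures text, all would be asked.

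**2. The plan's own figure.** Inputs: 28 per arm and two-sided 0.05 (Sample size justification); 20% versus 55% (Comments on power, hypercalciuria). No power is stated there, so the 80% of the primary outcome is assumed. The chi-square normal approximation gives 78.8%, which reproduces the claim closely. Exact Fisher gives 71.1%. Both tests are allowed for this outcome.

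**3. Dilution model (assumption).** A share q of children in both arms is above the limit before dosing and stays above it. Among the rest, new onset occurs at rate r0 (usual care) or r1 (high dose). Then:

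- observed rate = q + (1 − q)r
- observed difference = (1 − q)(r1 − r0)
- children per arm with a normal baseline = 28(1 − q), rounded

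The documents give no q, r0 or r1, so the results below are a range and not an estimate.

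**4. Results, exact two-sided Fisher, r0 = 0%, r1 = 25%.**

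| q | High-dose rate, all cases | All cases, usual care vs high dose | Power, all cases (28 per arm) | Normal baseline per arm | Power, new onset |
|---|---|---|---|---|---|
| 5% | 0.05 + 0.95 × 0.25 | 5% vs 28.75% | 53% | 27 | 70% |
| 10% | 0.10 + 0.90 × 0.25 | 10% vs 32.5% | 41% | 25 | 62% |
| 20% | 0.20 + 0.80 × 0.25 | 20% vs 40% | 28% | 22 | 68% |

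New-onset power is higher with 22 than with 25 children per arm because Fisher's test is discrete. The last column should be read as roughly 60 to 70%.

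**5. Other incident rates.**

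- r0 = 5%, r1 = 30%: 46% (all cases) versus 55% (new onset) at q = 5%, and 27% versus 51% at q = 20%.
- r0 = 5%, r1 = 40%, a true 35-point difference: 75%, 66% and 49% counting all cases at q = 5%, 10% and 20%, against 84%, 82% and 77% for new onset.

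**6. False-positive check.** With the same rate in both arms, from 5% to 30%, and 28 per arm, the Fisher comparison rejects with probability 0.001 to 0.027. This is below 0.05 throughout, so pre-existing cases do not produce a spurious drug signal.

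**7. Where restricting to a normal baseline does not help.** If a raised ratio before dosing does not persist, excluding those children only loses numbers: for 20% versus 45%, power falls from 43% (28 per arm) to 31% (22 per arm). If missing samples leave 15 per arm with a normal baseline, 0% versus 25% has 31% power, about the same as the 28% in the last row of the table.

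**The case against.** A reader might infer that pre-existing hypercalciuria is scored as a drug effect, or that the trial cannot separate background from drug. The documents do not support this. No individual case is attributed to study drug. Rates are compared between randomized, blinded arms, and the rationale for the usual-care arm includes measuring baseline risk for these events. At group level the concurrent control does the separating. Any elevated ratio, compared between arms, is a valid outcome.

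Nor do the documents show that a true effect is hidden. The 20% in the comments on power is a pre- or postoperative rate under usual care and would already contain pre-existing cases. Treating it as a pre-treatment prevalence that fully persists, with no new onset under usual care, is the most favourable case for using the baseline. The only anchor in the documents is the roughly 5% implied by the percentile limit, where the gap is 53% versus 70%.

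It would also be too strong to say that baseline urine is restricted to the least-exposed children. The procedures text says otherwise, and footnote a matches the blood rule closely enough to suggest a labelling slip. In a single-center trial the slip may be harmless in practice.

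Finally, analysis detail is often left to a SAP, and the secondary-outcomes text does allow regression. That answers only part of the point. The regression is conditional on an observed imbalance, whereas adjustment for a baseline measure of the same quantity gains precision without one. The contradiction between Table 4 and the text stands whatever a SAP says.

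**Conclusion.** The point holds in a limited form. Table 4 footnote a and the procedures text contradict each other on pre-treatment urine, and the hypercalciuria outcome as stated gives that planned ratio no role. The consequence is a smaller observed difference, by the factor (1 − q), and lower power. It is not bias toward a false drug effect.

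In the illustrations with 0% versus 25% new onset, the loss runs from 53% against 70% at 5% pre-existing to 28% against 68% at 20%. These figures assume 28 evaluable children per arm, full persistence of pre-existing positivity and a baseline from every child. Low persistence or many missing baselines would shrink or remove the gain. Replacing the outcome with new onset alone is therefore not justified. Reconciling the passages and using the baseline in an added analysis is worthwhile on a stated secondary safety objective.

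**What to change.** 1. Reconcile Table 4 with the procedures text: attach footnote a to the pre-treatment blood sample only, and show the urine sample as requested from all participants.
2. Keep the any-elevated-ratio comparison at the operating-room and first-postoperative-day samples, and state that it counts any elevated ratio, whether or not present before dosing.
3. Pre-specify an analysis of the log calcium:creatinine ratio, relative to the age limit, adjusted for the pre-treatment log ratio, with a missing-baseline indicator so that no child is dropped.
4. Add a supportive new-onset analysis in children with a normal baseline, and report how many in each arm had a baseline.

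The cost is a table correction and a few lines of analysis text, since the procedures text already plans the urine. The limitation is that initiation samples are optional, so some baselines will be missing.
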